#### Participant timeline {13}

Participant timeline is shown in Table 4.

**Table 4 Tab4:** Participant timeline

Assessment (A)		A1	Allocation	A2	Birth	A3	A4	A5	A6	A7
	Enrolment and screening			Post-allocation period						
Timepoint	Screening and Enrolment	Baseline		End of pregnancy		6–12 days	12 weeks	6 months	12 months	24 m
Screening form and eligibility checklist	X									
Demographic and socio-economic status		X								
Tracing and location information	X	X		X			X	X	X	X
GPS capture of home		X								
Allocation			x							
**Primary outcomes**										
BSID-III cognitive										X
EPDS									X	
**Secondary outcomes**										
EPDS	X			X			X			X
GAD-7		X		X					X	X
Maternal Antiretroviral treatment adherence		X		X			X		X	X
Exclusive Breastfeeding								X		
Infant immunisations							X		X	X
Infant diarrhoea							X	X	X	X
Cognitive and emotional stimulation (MICS)									X	X
Infant Behaviour (PSI/SF and Externalising subscale CBC)*									X	X
BSID-III language										X
Child Growth (weight and height)							X		X	X

#### Sample size {14}

The first primary outcome is the cognitive subscale on the BSID-III at 24 months of age. To achieve power of over 90% (two-sided *t*-test with a significance level of 0.05), and assuming an estimated difference of 6 points (SD 15), a total sample size of 396 women (198 per arm) is required. This calculation takes into account geospatial clustering (28 clusters per arm with an intra-cluster correlation coefficient (ICC) of 0.05) and ‘counsellor effect’ in the intervention arm (4 lay counsellors with an ICC of 0.05). To take account of attrition of up to 25%, a total sample size of 528 women is being recruited (264 per arm, 48–60 geospatial clusters, 9–11 women per cluster).

Using the EPDS assessment with a standard deviation of 5, with the same assumptions of clustering as above, a difference of 2 points between trial arms (not adjusting for baseline or repeated measurements) could be detected with 90% power and a 5% two-sided significance level. Analysis using repeated measures, taking into account within-participant correlation over time, would allow smaller differences to be detected with the same power

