### Trial design {8}

A cluster randomised controlled superiority trial with two parallel groups. The trial comprises 48–60 neighbourhood clusters, randomly allocated to the combined intervention or ESoC using a 1:1 allocation ratio with approximately 9–11 participants (mothers) per cluster, totalling 528 mother-infant pairs.

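### The stated 90% power for both primary outcomes does not follow from the printed clustering inputs: four counsellors at ICC 0.05 give about 71%

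*Protocol article*

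**What the plan says.** Sample size {14} of the protocol article gives every input. For the BSID-III cognitive score the aim is "To achieve power of over 90"%, two-sided, "with a significance level of 0.05", "assuming an estimated difference of 6 points (SD 15"). The result is that "a total sample size of 396 women (198 per arm) is required". The section says this figure includes two sources of clustering: "28 clusters per arm with an intra-cluster correlation coefficient (ICC) of 0.05", and a counsellor effect "in the intervention arm (4 lay counsellors with an ICC of 0.05").

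For the EPDS (SD 5) the section keeps the same clustering assumptions and says that a 2-point difference "could be detected with 90% power and a 5% two-sided significance level". It states that this excludes any gain from baseline adjustment or repeated measurements.

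Two other places bear on the point. Intervention description {11a} gives each woman one counsellor for all ten sessions and the booster. Statistical methods {20a} fits geospatial cluster and counsellor as random effects, with counsellor nested inside cluster.

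**The concern.** With 198 analysed women and four counsellors, each counsellor has about 50 women. An ICC of 0.05 in groups of that size is a large penalty, and it falls on the whole intervention arm. It is hard to see how it could leave power above 90% when the individually randomised calculation with the same numbers gives about 98%.

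At stake is how the result will be read. A reader of a null finding will lean on the stated power. If the Type II error is 29% and not 10%, that reader will take the null as stronger evidence of no effect than the design supports. This applies to both co-primary outcomes.

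**Working it through.** **Inputs** (all from Sample size {14}): 198 analysed women per arm; 28 clusters per arm, so 198/28 = 7.07 women per cluster; cluster ICC 0.05; 4 counsellors in the intervention arm, so 198/4 = 49.5 women each; counsellor ICC 0.05; difference 6, SD 15; two-sided 5%. The attrition step reproduces: 396/0.75 = 528.

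**Formula.** Power = Φ(δ/SE − 1.96), with SE² = (SD²/198) × (DE_int + DE_ctrl).

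**Looking for the plan's own figure.**
- No clustering: power 97.8%.
- Geospatial clustering only, both arms: DE = 1 + 6.07 × 0.05 = 1.304, SE = 1.72, power 93.6% (92.8% using t with 54 df).
- A separate, independent counsellor effect in each of the 28 clusters: intervention-arm ICC 0.10 within about 7 women, SE = 1.82, power 91.0% (90.0% using t with 54 df).

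Both clustered calculations agree with the claim. Neither has four counsellors as the unit.

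**With the four counsellors as stated.**
- DE_ctrl = 1 + 6.07 × 0.05 = 1.304; variance = 225 × 1.304/198 = 1.481.
- DE_int = 1 + 6.07 × 0.05 + 48.5 × 0.05 = 3.729; variance = 225 × 3.729/198 = 4.237.
- SE = √(1.481 + 4.237) = 2.39. For 90% power it would have to be 6/(1.96 + 1.28) = 1.85.
- Power = Φ(6/2.391 − 1.96) = 70.9%.
- Difference detectable with 90% power = 3.24 × 2.391 = 7.75 points.

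**EPDS.** 2/5 = 6/15 = 0.40, with the same clustering, so power is again 70.9%. The difference detectable with 90% power is 7.75/3 = 2.58 points.

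**Robustness** (two-sided, normal approximation, 198 per arm unless stated):

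| Variant with 4 counsellors at ICC 0.05 | Power |
|---|---|
| Counsellor term only in the intervention arm, control unclustered | 76.3% |
| Counsellor term only in the intervention arm, geospatial term in control | 73.5% |
| Main case, 24 or 30 clusters per arm | 69.9% or 71.3% |
| Multiplied design effects | 64.9% |
| Main case, all 264 per arm retained | 75.0% |

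A one-sided 5% test, which is not what the plan states, would give 80.6%.

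**Ceiling.** As the number of women grows without limit, SE² tends to 225 × (0.05/28 + 0.05/28 + 0.05/4) = 3.616, so SE = 1.90 and power is 88.4%. Under the stated assumptions no sample size reaches 90%.

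**What would give 90%.**
- With 4 counsellors, by counsellor ICC:

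| ICC | 0 | 0.005 | 0.008 | 0.01 | 0.02 | 0.03 | 0.05 |
|---|---|---|---|---|---|---|---|
| Power | 93.6% | 91.5% | 90.2% | 89.3% | 84.5% | 79.7% | 70.9% |

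- At ICC 0.05, by number of independent counsellors:

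| Counsellors | 8 | 12 | 20 | 22 | 28 |
|---|---|---|---|---|---|
| Power | 82.4% | 86.4% | 89.6% | 90.1% | 91.0% |

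**Sensitivity to few degrees of freedom.** Four counsellors supply 3 df. A Satterthwaite approximation gives 5.718²/(4.237²/3 + 1.481²/27) = 5.4 df and about 54% power by non-central t; a simulated Welch test gave 55%. For df from 3 to 6 the range is about 41% to 56%.

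**The case against.** The best defence is that the calculation matches the analysis model. Statistical methods {20a} nests counsellor within geospatial cluster, and a calculation built that way gives about 91%, which may be how the figure arose. That probably explains the number but does not justify it. Nesting gives the 28 intervention clusters 28 unrelated counsellor effects. The sample size section says there are four counsellors, so each serves about 28/4 = 7 clusters, and her women share her effect across all of them.

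Four might be the number in post at one time and not the total over the trial; the article does not say. But 12 counsellors would still give only 86%, and about 22 would be needed for 90%.

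The planned EPDS analysis uses baseline and repeated measures and may do better than 71%. That is fair as a comment on the analysis, but the gain cannot be quantified from the article and need not shrink the counsellor component. The stated 90% expressly leaves it out.

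A reader might also infer that true power is about 54%. The article does not support that as a headline. It names a two-sided t-test for the calculation and mixed models for the analysis, with no small-sample correction, so the figure depends on a method that the reviewer has to choose.

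Finally, recruitment closed in July 2021, and the 95% confidence intervals will show the precision achieved whatever power was stated. Both are true. They make this a correction to a reported planning figure, not to the estimand, test or data.

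**Conclusion.** Wrong as written. On its own inputs the section supports about 71% power for both primary outcomes (65% to 76% across reasonable two-sided ways of combining the clustering terms), with a ceiling of about 88%. The stated Type II error of at most 10% becomes about 29%. This rests on the normal approximation, equal cluster and counsellor caseloads, four counsellors in all, one counsellor per woman, and both ICCs at 0.05. Counting the few counsellor degrees of freedom lowers power further, but by an amount that depends on the method.

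The conclusion is about the stated figure under the stated assumptions. It does not show that the trial's real power is 71%: the true counsellor ICC is unknown, and with a value of about 0.008 or less the 90% would stand.

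**What to change.** Leave the sample size unchanged and amend the text.

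1. In Sample size {14}, do one of two things. Either restate power as about 71% for both primary outcomes, with differences detectable at 90% power of about 7.8 BSID-III points and 2.6 EPDS points (the latter before any gain from baseline or repeated measures). Or say that 90% holds only for a counsellor ICC of about 0.008 or less, and tabulate power for counsellor ICCs from 0 to 0.05.
2. If a small-sample figure is given, name the method and label it an approximate sensitivity value.
3. Reconcile Sample size {14} with Statistical methods {20a}. The counsellor effect should be shared across all the clusters that a counsellor serves, so counsellor is crossed with geospatial cluster and not nested within it. State whether four is the total number of counsellors over the trial.

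The cost is a few sentences, a short table and one change to the description of the random effects. The stated power becomes less favourable. No data collection changes.

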#### Recruitment {15}

Recruitment and screening take place from 15 DoH Primary Health Care Clinics within a sub-district in KwaZulu-Natal offering maternity services.

##### Recruitment strategy

The recruitment process is led by recruiters from the trial team with support from DoH antenatal nurses and clinic clerks.

Recruitment into the trial occurs through a four-stage process:
Identification of potential participants—Clinic records are reviewed by antenatal nurses and clinic clerks at antenatal clinics to identify HIV-positive, pregnant women (gestational age 23–33 weeks) over the age of 16 years. The nurses and clerks reassure the potential participants that their clinical care will not be compromised by participation.Referral to recruiter—If the identified potential participants consent, they are referred to a trial recruiter who explains the trial procedures and screens for additional eligibility criteria.Depression screen—Administration of the EPDS if the potential participant meets all other eligibility criteria.Consent processes—Written consent and scheduling of baseline assessment at home for participants who fulfil all inclusion criteria, including an EPDS ≥ 9.

The baseline assessment is conducted at the home at which point the GPS location is verified. The participant is randomised (based on their geospatial cluster) following the baseline assessment.

Only participants who were diagnosed with HIV at least 2 weeks previously and have been initiated on ART are recruited.

If during the screening or recruitment process a participant indicates thoughts of self-harm on the self-harm item of the EPDS, this initiates a risk management response and immediate notification is then made to the Trial Coordinator and Trial Psychologist. The Trial Psychologist then makes a psychological assessment in order to establish whether there is active suicidal intent or behaviours. It these are present, the psychologist undertakes initial management including telephonic follow-up at 24 h, 48 h and 72 h, and referral to the DoH Psychologist at the local hospital as appropriate. Following this management, if the potential participant is no longer at risk for self-harm, and still meets recruitment criteria, then they will be offered participation in the study.

### Assignment of interventions: allocation

#### Sequence generation {16a}

The unit of randomisation is the cluster using the geospatial location of the participant’s home. There are approximately 300 neighbourhoods in the region included in this trial; these are defined by geographical area as well as population density so that they are equivalent in terms of sample size. The distinct neighbourhoods have been merged into 48–60 clusters to ensure comparable clusters in terms of key indicators, including population size. This clustering approach, and the important role of randomisation in this trial, has been presented to, and approved by, the AHRI Community Advisory Board.

#### Concealment mechanism {16b}

Allocation concealment is ensured by a two-step enrolment procedure whereby neither the recruiter nor the assessor establishing eligibility know to which arm the clusters have been allocated.

#### Implementation {16c}

The 48–60 geospatial clusters are randomly allocated to the integrated intervention or ESoC with an allocation ratio of 1:1 using a random sequence generated by a senior statistician at the National Perinatal Epidemiology Unit (NPEU), University of Oxford (using Stata/SE version 13 for Windows). The randomisation schedule is sent to AHRI using a secure web link and implemented by the local data management team. None of these parties is involved in the implementation of trial activities (recruitment, assessments, therapy).

### Assignment of interventions: blinding

#### Who will be blinded {17a}

Participants are not informed at enrolment as to which arm they are allocated to ensure the blindness of the recruiters and assessors. Rather, participants are informed that a trial counsellor will contact them. The intervention counsellors or the ESoC caller reveal the arm to which the participant has been allocated when they first make contact.

The recruiters and assessors are blinded to the treatment allocation arm. Furthermore, the assessors are independent of the lay counsellors performing the counselling sessions and blind to treatment allocation. The two primary endpoints are assessed by different independent assessors (at 12 and 24 months).

#### Procedure for unblinding if needed {17b}

In the event of inadvertent unblinding of an assessor, standard operating procedures are in place to reduce the impact and ensure that the assessor is never allocated to the given participant in future assessments.

##### Minimisation of contamination

Recruitment staff are located at clinics whilst intervention staff operate from a separate AHRI campus to minimise contact between recruitment and other staff. ESoC caller and lay counsellors operate separately within different scopes of work in distinct offices, are line-managed and supervised by different individuals, use separate transport services and attend separate meetings to reduce the risk of unblinding. They are trained not to share information that could compromise the blinding or the integrity of the trial. Any instances of unblinding are recorded and assessed at the conclusion of the trial.

### Data collection and management

#### Plans for assessment and collection of outcomes {18a}

Participants in both arms receive 6 assessments following the baseline assessment: (1) end of pregnancy; (2) 6-day postnatal screener, (3) 12-week postnatal, (4) 6 months; (5) 12 months, (6) 24 months. The points at which primary and secondary outcome data are collected are outlined in Tables 1, 2, and 3. Assessments take place at home, except for the 24 month assessment, including the primary endpoint BSID-III assessment, which takes place in participating clinics.

Table 5 outlines the standardised data collection tools used in the study. Below we outline tools specific to this study.

**Table 5 Tab5:** Data collection tools

Instrument	Description	Outcome	Contextual validity
The Bayley Scales of Infant Development-Third Edition (BSID-III) [62]	A comprehensive objective assessment administered face-to-face by a qualified independent assessor to assess child development. Only the cognition and language subscales are administered.	Child cognitive and language development	Validated in South Africa [63, 64] with reported values similar to the reference population in the USA [62].
Edinburgh Postnatal Depression Scale (EPDS) [65]	10-item questionnaire of perinatal depressive symptoms over the last 7 days assessed on a scale of 0 to 3.	Maternal depressive symptoms	Widely used and validated in Africa and South Africa, including use amongst antenatal populations [66]. Has been validated in the study population against a structured clinical interview for depression (DSM-IV) showing good specificity (93%) and sensitivity (68%) for detecting clinical depression [67, 68]
Child Behaviour Checklist (1.5-5-year-old) [69]	Externalising subscale (attention problems and aggressive behaviour syndrome scales) of the CBCL. 24 items, assessed on a scale of 0 to 2. Parental self-report.	Child externalising behaviour	Has been shown to be reliable in Africa [70], and to have high (> 90%) sensitivity and specificity for identifying behavioural emotional problems compared to a clinical diagnosis by a psychiatrist in other LMICs [71] Widely used and well-validated in South Africa [72, 73].
Parenting Stress Index Short Form [74, 75]	Measure of parenting stress related to three domains: the parental role, the parent-child relationship, and the degree to which the parent finds the child difficult. The scale comprises 36 statements, which are scored 1 (strongly disagree) to 5 (strongly agree) and can be summed to reflect the total score for each domain.	Maternal perception of child behaviour (Dysfunctional Interaction and Difficult Child subscales)	Has been shown to be reliable in South Africa [76]
Brief Rumination Response Scale	A 5-item questionnaire assessing depressive rumination assessed on a scale of 0 (never) to 4 (always).	Maternal rumination	A validated and reliable measure of depressive rumination [61, 77]
The Generalized Anxiety Disorder Scale (GAD-7)	7-item questionnaire assessing symptoms of generalised anxiety disorder over the previous 2 weeks. Scores	Maternal anxiety	Has been widely used in the study setting and has shown good reliability [76, 78].
Multiple Indicator Cluster Survey (MICS)	Specific questions from the Early Child Development module of the UNICEF ‘Multiple Indicator Cluster Surveys’ (MICS) under five are used to assess cognitive and emotional stimulation at home. Items are mostly scored on a dichotomous scale of 0 and 1 except for the question about how many children’s books or picture books a mother has for her child (0 = none, 1 = a number of books and 2 = ten or more books).	Cognitive and emotional stimulation.	Validated survey used in over 100 countries over the past two decades, also used in large scale surveys in 27 African countries [79, 80].

### Maternal recognition of infant faces and sounds

The participant’s ability to accurately interpret and respond to infants’ emotional cues is assessed using a subset of stimuli baby faces developed by rigorous validation methods in Brazil [81] and a sample of standardised baby vocalisations [82, 83]. Mothers are asked to indicate their interpretation of both the facial expressions (‘happy’, ‘neutral’, ‘sad’) and the vocalisations (positive ‘laughs’ neutral ‘babbles’ and ‘negative ‘cries) on an electronic tablet screen using a vertical visual analogue scale. The faces used for this sample include Caucasian, African and mixed-race infant faces and the images are presented in greyscale and matched in size and luminosity [84]. The task takes around 15 min to complete.

### Economic evaluation

Costing is conducted from a societal perspective, including financial costs to providers, opportunity costs of diverted provider resources (such as time of staff not paid on the trial, space) and financial (e.g. travel, time off work) and opportunity costs (e.g. time away from unpaid productive activities) to participants. We distinguish between research costs and operational costs to allow estimation of the cost of replication in non-research settings. The analysis involves three levels with increasing complexity. The first level involves a cost-utility analysis of the intervention with the primary and secondary outcome included in turn: the cost per improvement in cognitive development; the cost per improvement in maternal depression. The second level involves cost-effectiveness analysis using disability-adjusted life years (DALYs) averted. Improvements in child cognitive development and maternal depression are converted to DALYs based on assumptions regarding the duration of the observed benefit. The cost per DALY is then calculated. The third level compares costs to a vector of benefits, including indicative estimates of long-term gains (based on simple models), such as improved education outcomes and increased income in adulthood.

### Nested qualitative study

A qualitative sub-study is conducted alongside the trial, using semi-structured interviews with both the lay counsellors who delivered the intervention and with a sample of participants from each study arm. The sub-study aims to investigate the acceptability, challenges, enablers and potential benefits of the combined intervention compared to ESoC. The sub-study also investigates the acceptability and effectiveness of the therapist training and therapy supervision for this intervention. The data will be analysed using grounded theory principles and thematic content analysis [85, 86].

### Plans to promote participant retention and complete follow-up {18b}

We have developed a standard operating procedure to guide and promote retention and follow-up. This includes maintaining a regular schedule of assessments. Tracing and follow-up methods include text, telephone calls and in-person track and tracing. Participants are encouraged to notify the trial staff if they change their telephone number or address. Retention in the study community in previous clinical trials using these strategies has resulted in high retention rates. If participants discontinue the intervention (therapy/ESoC), they continue to receive assessments, including the primary outcome assessments (providing their consent).

### Data management {19}

Study data are collected and managed using a secure, web-based data collection platform on encrypted tablet computers which are securely uploaded to a central server hosted at AHRI. The platform is a secure, web-based software platform designed to support data capture for research studies, providing (1) an intuitive interface for validated data capture; (2) audit trials for tracking data manipulation and export procedures; (3) automated export procedures for seamless data downloads to common statistical packages and (4) procedures for data integration and interoperability with external sources. The tablets are encrypted, and all documents are stored safely under confidential conditions. On all trial-specific documents, other than the signed consent forms, the participant is referred to by the trial participant number, not by name.

